## Abstract

**Background:** The morphology and functional severity of coronary stenosis show poor correlation. However, in clinical practice, the visual assessment of the invasive coronary angiography is still the most common means for evaluating coronary disease. The fractional flow reserve (FFR), the coronary flow reserve (CFR), and the resting full-cycle ratio (RFR) are established indices to determine the hemodynamic significance of a coronary stenosis.

**Design/Methods:** The READY register (NCT04857762) is a prospective, multicentre register of patients who underwent invasive intracoronary FFR and RFR measurement. The main aim of the registry is to compare the visual estimate of coronary lesions and the functional severity of the stenosis assessed by FFR, as well as the RFR pullback. Characterizations of the coronary vessel for predominantly focal, diffuse, or mixed type disease according to visual vs. RFR pullback determination will be compared. The secondary endpoint of the study is a composite of major adverse cardiac events, including death, myocardial infarction, and repeat coronary revascularization at 1 year. These endpoints will be compared in patients with non-ischemic FFR in the subgroup of cases where the local pressure drop indicates a focal lesion according to the definition of ΔRFR > 0.05 (for <25 mm segment length) and in the subgroup without significant ΔRFR. In case of an FFR value above 0.80, an extended physiological analysis is planned to diagnose or exclude microvascular disease using the CFR/FFR index. This includes novel flow dynamic modeling for CFR calculation (CFR_p−3D_).

**Conclusion:** The READY register will define the effect of RFR measurement on visual estimation-based clinical decision-making. It can identify a prognostic value of ΔRFR during RFR pullback, and it would also explore the frequency of microvascular disease in the patient population with FFR > 0.80.

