## Study Objectives and Design

The “*Anatomical assessment vs. pullback REsting full-cycle rAtio measurement for evaluation of focal and Diffuse coronarY disease (READY)*” register is an investigator-initiated, prospective, and multicentre observational study. Three hundred patients with coronary stenoses between 40 and 90% in diameter and clinical indication of intracoronary physiological assessment are planned to be included.

The study is approved by the Hungarian Institution of Pharmacy and Nutrition (OGYÉI/61148/2018) and registered on the ClinicalTrials.gov (NCT04857762). All the included patients will sign an informed consent form to participate in the registry. Execution of the study is supported by an unrestricted grant provided by the PremierGMed Cardio Ltd.

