### Statistical Analysis

Descriptive statistics are planned as mean and SD, median (interquartile range) of the measured RFR and FFR values. Categorical variables will be compared with the Pearson χ^2^ test for focal/ diffuse/mixed type categorizations of the coronary disease by visual and physiological evaluations.

Correlation among variables will be determined by calculating Spearman ρ correlation coefficient.

Kaplan-Meier curves will be used to graphically display adverse events by focal lesion (ΔRFR ≥ 0.05/ 25 mm) and without focal lesion (ΔRFR < 0.05/ 25 mm) arms in the cases with FFR > 0.80. We plan to use survival analytic techniques such as a log-rank test to estimate the difference between the 2 subgroups.

The required sample size for the statistically significant (*p* < 0.05) difference with 80% power of the Kaplan-Meier curves of adverse events by focal lesion (ΔRFR ≥ 0.05/ 25 mm) and without focal lesion arms are 425, assuming 10 and 2% event rate in the two subgroups, respectively.

ROC analysis will be used to determine an optimal clinical cut of value, of ΔRFR (together its sensitivity and specificity) to predict a secondary endpoint at 1 year.

All analyses will be performed by using the Medcalc statistical software (MedCalc Software Ltd, Belgium).

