**Figure 5 F5:**
[figure not shown]
Flow-chart of the proposed clinical decision-making process according to the results of physiological measurements.

In the secondary endpoints of the register, we focused on the patient population with non-ischemic FFR value. During the 1-year follow-up, the prognostic value of the focal lesions (ΔRFR > 0.05) for cardiac adverse event will be investigated in this subgroup.

The characterization of the microvascular capacity may have also paramount relevance in cases of negative (>0.80) FFR values. If the extended physiological assessment shows low CFR/FFR index or MRR value, then microvascular disease is diagnosed with the impact on appropriate specific pharmaceutical treatment (20).

This relatively simple, combined resting and hyperemic assessment can provide a comprehensive physiological evaluation of the coronary disease with important treatment consequences.

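### The prognostic comparison of focal with non-focal ΔRFR names only an unadjusted log-rank test, which gives no effect estimate and cannot separate ΔRFR from FFR within the FFR > 0.80 subgroup

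*Protocol article*

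**What the plan says.** The design is stated under Study Objectives and Design: the "register is an investigator-initiated, prospective, and multicentre observational study". The Abstract calls it a "prospective, multicentre register of patients who underwent invasive intracoronary FFR and RFR measurement", so FFR is on record for every patient.

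The outcome comparison is described in Statistical Analysis. Kaplan-Meier curves are to be drawn for patients with a focal lesion and those "without focal lesion (ΔRFR < 0.05/ 25 mm) arms in the cases with FFR > 0.80". The test follows: "We plan to use survival analytic techniques such as a log-rank test to estimate the difference between the 2 subgroups". The sample size of 425 is set for a "statistically significant (*p* < 0.05) difference" at 80% power, assuming event rates of 10% and 2%. ROC analysis is then to look for a ΔRFR cut-off. The only other mention of association is general: "Correlation among variables will be determined by calculating Spearman ρ correlation coefficient".

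The Discussion gives the intended inference in FFR-negative patients: "the prognostic value of the focal lesions (ΔRFR > 0.05) for cardiac adverse event will be investigated in this subgroup".

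The article names no regression model, stratification or covariate. FFR enters the outcome comparison only through the restriction to values above 0.80.

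**The concern.** There are two separate problems.

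The first is a mismatch between aim and method. The sentence promises to estimate a difference, but the one technique it names tests a null hypothesis and returns no effect size. With few events, a bare p-value tells the reader very little.

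The second is interpretation. FFR and ΔRFR are pressure measurements from the same vessel. If patients with a focal resting drop also tend to have lower FFR within the 0.80 to 1.00 range, and if lower FFR in that range carries more risk, the log-rank test will attribute to ΔRFR some risk that FFR already conveys. The Background section hopes the register will give guidance for patients with negative FFR and a focal pressure drop. A reader will want to know whether the focal drop adds anything to an FFR value already in hand, and the crude contrast cannot show that.

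**Working it through.** **1. The plan's own figure.** A two-sided 5% comparison of 10% with 2% at 80% power, with a 1:4 focal to non-focal split and a continuity correction, needs 85 + 340 = 425 patients. This matches the article, though it states neither the split nor the correction. The figure rests on the crude contrast. The implied hazard ratio is ln(0.90)/ln(0.98) = 5.2.

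**2. Is a link between FFR and ΔRFR plausible from the document?** The pressure-bounded CFR formula in the extended physiological assessment has the upper bound CFR ≤ hyperaemic Δp / resting Δp, so hyperaemic Δp ≥ CFR × resting Δp. With FFR = 1 − hyperaemic Δp / aortic pressure, and aortic pressure taken as unchanged:
- resting drop 5% of aortic pressure, CFR 1.5: FFR ≤ 1 − 0.075 = 0.925
- resting drop 5%, CFR 2: FFR ≤ 0.90
- resting drop 3%, CFR 2: FFR ≤ 0.94

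The 3% case matters because RFR takes the largest resting difference in the cycle (Background), so the mean drop is smaller than ΔRFR. The drops and CFR values are assumptions. A focal drop thus caps FFR below 1.00. One feature works the other way: the non-focal group can include purely diffuse disease, which also lowers FFR and narrows the gap.

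**3. Size of the possible bias if ΔRFR has no effect.** Spurious hazard ratio ≈ h^(gap/0.01), where h is the hazard ratio per 0.01 lower FFR. Both inputs are assumed.

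| h | gap 0.03 | gap 0.06 |
|---|---|---|
| 1.05 | 1.16 | 1.34 |
| 1.10 | 1.33 | 1.77 |
| 1.15 | 1.52 | 2.31 |

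With h = 1 or no gap, the result is 1.00.

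**4. Effect on the test.** Simulation with no true ΔRFR effect, 1,500 runs per scenario, assumed latent FFR-ΔRFR correlation 0.3 to 0.7, and assumed hazard ratio 1.5 to 2 per 0.05 lower FFR (about 1.08 to 1.15 per 0.01):

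| Patients, focal share, event rate | Log-rank rejects | Cox with FFR rejects |
|---|---|---|
| 425, 40%, 6% | 8–47% | 4–6% |
| 425, 20%, 3.6% | 7–32% | 2–3% |
| 200, 40%, 5.2% | 7–24% | 2–4% |

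At 425 patients with 40% focal, zero correlation or no FFR effect left the log-rank test at about 5%.

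**5. Precision available.** Enrolment is 300 before restriction to FFR > 0.80. If 150 to 195 are FFR-negative (assumed 50–65%) and the split is 1:4 (assumed), expected events are 30 × 0.10 + 120 × 0.02 = 5.4, up to 39 × 0.10 + 156 × 0.02 = 7.0. At a 1:1 split they would be 9 to 12. With 5.4 to 7.0 events, SE(log HR) ≈ 1/√(events × 0.2 × 0.8) = 1.08 to 0.94, so the crude 95% interval extends by a factor of 8.2 to 6.4 each way. Adjustment multiplies the SE by 1/√(1 − R²), where R is the assumed correlation of focal status with FFR. At R = 0.5 (×1.15) the factor becomes about 8 to 11, and at R = 0.7 (×1.40) about 13 to 19. Events for 80% power at hazard ratio 5.2 and a 1:4 split rise from 18 (R = 0) to 20, 24 and 36 (R = 0.3, 0.5, 0.7).

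**The case against.** The strongest reply is that the article asks a narrower question: whether a focal drop marks higher risk among patients whose FFR is negative. FFR is used as a clinical dichotomy, restriction to FFR > 0.80 is the control, and a crude comparison answers that question. The one reference to additive value, in the Discussion, is relative to visual estimation and not to FFR. This stands, and it is why the crude analysis should be kept. It does not supply the missing estimate, and it gives no basis for reading a positive result as information beyond FFR.

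A reader might infer that the result is in fact confounded by FFR, or that focal patients will cluster just above 0.80. The documents do not support either. They give no FFR-ΔRFR correlation and no relation of FFR to outcome above 0.80. The bound in step 2 of the working makes a link plausible but does not size it. Nor does the bias computed under these assumptions explain the planned effect: 2.3 is well short of 5.2.

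It can also be said that the words *such as* leave regression open and that a fuller plan may specify it. Silence on covariates in a condensed article is indeed no fault. What remains is that the one method named does not do what its sentence says.

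Finally, a two-term Cox model on so few events can hardly separate two correlated predictors. That is correct, and it limits what the adjusted model can deliver. It argues for placing that model beside the crude result, not in its place.

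**Conclusion.** The point holds in a limited form. It is certain from the text that the only named between-group method is an unadjusted test that estimates nothing, applied to non-randomised groups, although FFR is recorded for everyone. It is possible, but not shown, that the crude contrast is partly an FFR effect. The hazard ratio of 1.2 to 2.3 and the inflated rejection rates rest wholly on assumed links. The 47% upper end belongs to 425 FFR-negative patients under the strongest assumptions and should not be carried over to a register of 300. At 200 patients the corresponding range was 7–24%. The endpoint is secondary, so this is a change that should be made and not a threat to the primary aim.

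**What to change.** - Keep the Kaplan-Meier curves and the log-rank test as the crude analysis.
- Report the 1-year Kaplan-Meier risk difference and the crude hazard ratio, each with a 95% confidence interval, and reword the sentence so that the log-rank test tests and these quantities estimate.
- Pre-specify beside them a Cox model with focal status and continuous FFR, penalised (for example Firth, with profile-likelihood intervals) if events are few. FFR is the natural single covariate because it defines the subgroup, is measured in everyone, and few events leave little room for more.
- State that prognostic value beyond FFR will be claimed only from the adjusted estimate.
- Amend the commitment to run all analyses in MedCalc if that package cannot fit the penalised model.

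No new data are needed, and the work is a short addition to the analysis. The real cost is precision: the adjusted interval will be wide and may be uninformative at the event counts in step 5 of the working. Other baseline risk factors also remain unadjusted, so even the adjusted estimate should be reported as an association.

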Such a prognostic pressure-drop cut-off value for invasive hyperemic or non-hyperemic pullback measurements has not yet been established. We defined the focal disease criterion as ΔRFR >0.05 for <25 mm segment length which is the same gradient for a 1 mm unit (>0.002/mm), similarly as it was defined for the iFR. We set out to test this threshold for prognostic value in our registry during the follow-up of patients with negative FFR but positive focal ΔRFR (4).

While the main aim of the READY registry is to characterize the effect of RFR measurement on the visual estimation-based clinical decision-making, it may also provide guidance in cases with a non-ischemic FFR but with focal pressure drop (ΔRFR > 0.05).

We plan to analyze the follow-up data at 1 year not only according to the pre-specified categories but also to determine potential alternative cut-off values using receiver-operator characteristic (ROC) analysis. In addition, it will also explore the frequency of microvascular disease in the patient population with FFR > 0.80.

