**Figure 3 F3:**
[figure not shown]
Flow chart of the comparison of the visual assessment and the results of the RFR measurement.

Secondary endpoints in the subgroup of patients with negative FFR:

2. Secondary endpoint is defined only in the subgroup of patients with negative FFR as a composite of major adverse cardiac events, including death, type 1 myocardial infarction and coronary revascularization on the target vessel at 1 year. Type 1 myocardial infarction of the target vessel is defined according to the ESC classification (10). Revascularisation of the target vessel considered to be the composite secondary endpoint during the follow up.3. Clinical endpoints will be compared in patients with non-ischemic FFR and the subgroup of cases where the local pressure drop indicates a focal lesion according to the definition of ΔRFR > 0.05 (for <25 mm segment length), and the subgroup without significant ΔRFR.4. In the extended physiological sub-study, in cases where information regarding the microvascular state is desirable (i.e., patients with non-pathological FFR), the intracoronary average pressure values and the data of the 3D coronary reconstruction will be used for the calculations of coronary flow reserve (CFR) and the microvascular resistance reserve (MRR) (11–14). The rate of microvascular dysfunction will be determined in the investigated patient population (Figure 4).

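### The ROC-derived ΔRFR cut-off and its accuracy would come from the same roughly 5 to 18 events, so its sensitivity would be overstated and its location imprecise

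*Protocol article*

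**What the plan says.** The operative sentence in Statistical Analysis begins: "ROC analysis will be used to determine an optimal clinical cut of value". The threshold sought is one for ΔRFR, its accuracy in both directions is to be given with it, and the outcome it should predict is the clinical composite after one year of follow-up. The Background describes the same analysis more cautiously. There the follow-up data will be analysed by the pre-specified categories and also used to "determine potential alternative cut-off values using receiver-operator characteristic (ROC) analysis".

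Three other statements fix how much information the analysis will have:
- Study Objectives and Design plans "Three hundred patients with coronary stenoses between 40 and 90% in diameter", whatever their FFR.
- The list of secondary endpoints, after Figure 3, says "Secondary endpoint is defined only in the subgroup of patients with negative FFR".
- The sample-size paragraph works from 80% power, "assuming 10 and 2% event rate in the two subgroups, respectively".

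The article gives no event count or precision target for the ROC analysis and names no rule for what makes a cut-off optimal.

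**The concern.** When a cut-off is chosen because it separates events from non-events best in one set of patients, its accuracy in those patients is on average better than in new patients. The gap grows as events become fewer. Here the events are few, the accuracy figures are to be reported with the cut-off, and the sentence that governs the analysis calls the result an optimum for clinical use.

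The Background says that no prognostic pressure-drop threshold has yet been established for invasive pullback, so a published value could be taken up as the reference. The Discussion adds that RFR-based lesion typing could influence the choice of treatment. Readers would then be relying on a sensitivity that is too high, at a cut-off the data may be unable to distinguish from the pre-specified 0.05.

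**Working it through.** **The plan's own figure.** The only sample size given is 425, for the log-rank comparison of focal and non-focal subgroups. It is reproduced by a continuity-corrected comparison of two proportions, two-sided 0.05, 80% power, with a 1:4 focal to non-focal split (the split and the sidedness are not stated):
- Pooled rate: (0.10 + 4 × 0.02)/5 = 0.036.
- Uncorrected n (focal): [1.96·√(1.25 × 0.036 × 0.964) + 0.8416·√(0.09 + 0.0196/4)]² / 0.08² = 69.6.
- Corrected n: (69.6/4)·[1 + √(1 + 10/(4 × 69.6 × 0.08))]² = 84.5, rounded up to 85.
- Total: 85 + 340 = 425.

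This figure does not size the ROC analysis, but a 1:4 split corresponds to a focal share of 20%, the lower end of the range used below.

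**Expected events.** Events = N × [s × 0.10 + (1 − s) × 0.02], where N is the number of FFR-negative patients and s the focal share. Both are assumptions.

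| FFR-negative N | s = 20% | s = 50% |
|---|---|---|
| 150 | 5.4 | 9.0 |
| 200 | 7.2 | 12.0 |
| 300 (all enrolled) | 10.8 | 18.0 |

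**Discrimination implied by the planned rates.** For the fixed 0.05 threshold:
- s = 20%: sensitivity 0.020/0.036 = 0.56, false-positive rate 0.180/0.964 = 0.19, Youden index J = 0.37.
- s = 50%: sensitivity 0.050/0.060 = 0.83, false-positive rate 0.450/0.940 = 0.48, J = 0.35.

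Under an equal-variance binormal marker, AUC 0.75 gives a maximum J of 2Φ(0.954/2) − 1 = 0.37. An AUC of about 0.75 is therefore a fair reading of the planning assumptions.

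**Simulation.** ΔRFR was drawn as log-normal (median 0.04, log-SD 0.6), rounded to 0.01, and the cut-off with maximum J was chosen in each run. The distribution and the Youden rule are assumptions. True sensitivity is that of the chosen cut-off in new patients, averaged over runs. Repeat runs move these values by about 0.01.

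| N, events | Apparent sensitivity | True sensitivity | Excess |
|---|---|---|---|
| 150, 5 | 0.79 | 0.61 | 18 points |
| 300, 11 | 0.73 | 0.63 | 10 points |
| 300, 18 | 0.72 | 0.65 | 7 points |

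- Specificity: apparent and true values differ by 0.01 or less.
- Chosen cut-off, 95% of runs: lower limit about 0.03 to 0.04, upper limit about 0.10 to 0.13.
- Without rounding, the excess is larger: 0.84 against 0.62 (150, 5), 0.78 against 0.64 (300, 11) and 0.75 against 0.64 (300, 18).
- With a marker of no value (AUC 0.50, true J = 0), the apparent J of the rounded marker is 0.20 at 5 events in 150 and 0.11 at 18 in 300.

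**Precision.** Exact 95% intervals for an observed sensitivity near 80% are 28 to 99% for 4/5, 52 to 98% for 10/12 and 52 to 94% for 14/18.

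**The case against.** The strongest reply is that this is a condensed article. Resampling and optimism correction are commonly left to a full protocol or SAP, and neither is shown, so a reader who infers that no validation is planned goes beyond the text. That stands. The point rests only on what the article does fix: one best cut-off, with accuracy figures, from this registry's own events.

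Several stronger readings are also tempting and do not hold:
- *The cut-off would be mostly noise.* At the plan's own rates this fails. The chosen cut-off has a true J of 0.31 to 0.34 against a maximum of about 0.37, even at the smallest event counts.
- *All of its accuracy is inflated.* Specificity is essentially unbiased, because about 94 to 96% of patients are event-free.
- *ROC would mishandle patients lost before 1 year.* The article gives neither a loss rate nor a rule for such patients, so nothing supports this.
- *The plan itself implies only 5 to 9 events.* That needs about half of patients to be FFR-negative, which is not stated. The defensible range is 5 to 18.

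It can also be said that the analysis is already exploratory, since the Background speaks of potential alternatives and 0.05 remains the pre-specified threshold. This is partly right: the focal versus non-focal comparison at 0.05 and the primary endpoint carry none of this optimism. But the governing sentence in Statistical Analysis has no exploratory label and makes the stronger claim.

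**Conclusion.** The point holds in this limited form. Carried out as written, the ROC analysis would overstate sensitivity by about 7 to 18 percentage points, and the Youden index with it. It would leave specificity nearly unchanged and place the cut-off anywhere from about 0.03-0.04 to 0.10-0.13. Since 0.05 lies inside that interval, the data would be unlikely to show that a new cut-off differs from the pre-specified one.

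These sizes depend on the assumed FFR-negative share (50 to 100%), focal share (20 to 50%), AUC of about 0.75, Youden rule and marker distribution. The direction does not depend on them: even if every enrolled patient were FFR-negative and half were focal, only 18 events would be expected. The gap between the 425 required and the 300 planned contributes to the scarcity but is a separate matter. Even 425 FFR-negative patients would give only 15.3 to 25.5 events.

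**What to change.** In Statistical Analysis:
1. Report the AUC of continuous ΔRFR with its 95% confidence interval.
2. Report sensitivity and specificity at the pre-specified 0.05 with exact 95% intervals. No search is involved there, so they carry no selection optimism.
3. If a data-derived cut-off is given, name the rule that selects it. Add a bootstrap percentile interval and optimism-corrected sensitivity and Youden index, repeating the whole cut-off search in each resample.
4. Replace the description of the cut-off as a clinical optimum with exploratory wording that agrees with the Background.

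Recruitment, measurement and follow-up do not change. The cost is a bootstrap script, possibly outside the one statistical package the article names, and reported accuracy that will look less favourable.
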